#### Data collection

Data within this feasibility study will predominantly be collected at three main time points: baseline, post-intervention, and follow-up (Table 2).

##### Baseline assessment

Participant’s baseline socio-demographic and information for the patient-centred outcomes of the study will be collected between 12 days and 36 h prior to the commencement of the 6-week intervention. One repetition maximum (1RM) for all of the resistance training equipment utilised within the resistance training intervention will also be assessed during this time period (after all baseline testing has been completed, and at least 18 h after baseline testing which requires physical exertion, which may impact on the accuracy of the 1RM measurements).

##### Follow-up testing

Follow-up testing will be conducted 6 weeks post-intervention cessation for the feasibility and patient-centred outcomes of the study. All data will be gathered within a period of approximately 12 days from all participants.

Adherence rates in the intervention group will be recorded as the number of repetitions completed in a set (90% required for adherence to that exercise), and then the number of exercises for which there was a 90% adherence. If participants meet these parameters for each exercise session, they will be considered to be in 100% adherence to the intervention. For example, if a participant performs 95% of all exercises in one session, then they will be considered to be in adherence for that session. If they then continue this level of adherence for the remaining 41 sessions, they will have a 100% adherence. If a participant adheres to 95% of the intervention for 36 sessions, but only 80% for 6 sessions, then they will have an 86% adherence rate. Ninety percent of all exercises performed within that session will signify adherence to that session. Adherence rates, whether very high or somewhat low may signify that the intervention may have been too demanding, too easy or optimal. Information will also be collected throughout the study related to uptake and retention rates.

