### Intervention

The intervention within this study will be comprised of a moderately intensive, 35 min per session, 3–4 sessions per week, 6-week, machine-based resistance training intervention. The sessions will be conducted in groups of approximately six individuals in the form of a group exercise circuit. Study participants will perform exercises predominantly targeting the lower limbs (but also upper limbs and core) on six separate pieces of resistance training equipment: leg extension, leg curl, leg press, chest press, back row, seated abdominal crunch, and thigh abduction/adduction training machines (HUR Ltd., Helsinki) (Fig. 2).

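### With six to eight exercises per session, the 90% session-adherence rule requires every exercise, so one missed machine fails the whole session

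*Protocol article*

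**What the plan says.** The adherence definition is in the protocol article under Data collection, Follow-up testing. It has two levels.

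- **Exercise level:** the measure is "the number of repetitions completed in a set (90% required for adherence to that exercise").
- **Session level:** the unit is a count of exercises, "and then the number of exercises for which there was a 90% adherence", and the threshold is "Ninety percent of all exercises performed within that session will signify adherence to that session".

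The section illustrates the rule twice. First, "if a participant performs 95% of all exercises in one session, then they will be considered to be in adherence for that session". Second, a participant who adheres to "95% of the intervention for 36 sessions, but only 80% for 6 sessions, then they will have an 86% adherence rate".

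The number of exercises comes from the Intervention section, which describes "six separate pieces of resistance training equipment: leg extension, leg curl, leg press, chest press, back row, seated abdominal crunch, and thigh abduction/adduction training machines". The stated count is six, but the list has seven names. The same section caps group size at six because of the number of machines, which agrees with the stated count. It also gives 21 sessions over the 6 weeks, and Table 2 matches that.

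Adherence is listed in Table 1 as a method of assessment for Demand and for limited-efficacy testing. Follow-up testing adds that a high or low rate may show whether the programme was pitched too hard, too easy or about right.

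**The concern.** A 90% threshold, illustrated with sessions at 95% and 80%, suggests a graded scale on which a small shortfall is tolerated. With so few exercises in a session, the attainable percentages are coarse, and none may lie between 90% and 100%. If so, the session rule is stricter than it looks.

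This affects how the result is read. A resident who comes to every session but leaves out one station suggests that the station may need adapting. A resident who does not come suggests lack of demand. If both can receive the same adherence rate, the rate is a poor guide to how demanding the programme is, and informing the future trial on that question is one of its stated uses.

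**Working it through.** **Inputs.** Session threshold 90% and repetition threshold 90% (Follow-up testing); six machines stated and seven named (Intervention); 21 sessions (Intervention, Table 2). Eight exercises is the count if abduction and adduction on the last machine are taken separately.

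**1. The plan's own figure.** Adherent sessions ÷ all sessions = 36/(36 + 6) = 36/42 = 85.7%, which rounds to the stated 86%. The figure reproduces, and it confirms that a session at 80% scores as a failure and one at 95% as a pass. But the example assumes 42 sessions, whereas Table 2 gives 3 + 4 + 3 + 4 + 3 + 4 = 21. Six failed sessions out of 21 would give 15/21 = 71.4%.

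**2. What 90% requires.** For *m* exercises, find the smallest whole *k* with *k*/*m* ≥ 0.90, and the share left after one miss, (*m* − 1)/*m*.

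| Exercises *m* | Needed for ≥ 90% | Share after one miss | Share after two misses |
|---|---|---|---|
| 6 | 6 | 5/6 = 83.3% | 4/6 = 66.7% |
| 7 | 7 | 6/7 = 85.7% | 5/7 = 71.4% |
| 8 | 8 | 7/8 = 87.5% | 6/8 = 75.0% |
| 9 | 9 | 8/9 = 88.9% | 7/9 = 77.8% |
| 10 | 9 | 9/10 = 90.0% | 8/10 = 80.0% |

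With six, seven or eight exercises every one is needed. One miss is first tolerated at ten. Neither 95% nor 80% is an attainable session value with six, seven or eight.

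**3. Consequence for one resident.** A resident attends all 21 sessions, meets the repetition rule on five of six machines and omits the sixth each time. Exercises done: 5/6 = 83.3%. Adherent sessions: 0/21 = 0%. A resident who attends none also scores 0/21 = 0%.

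**4. If sets were counted instead.** The text shown does not give sets per machine, so two and three are assumed, equal across machines.

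| Machines | Sets each | One set missed | One whole machine missed |
|---|---|---|---|
| 6 | 2 | 11/12 = 91.7% | 10/12 = 83.3% |
| 6 | 3 | 17/18 = 94.4% | 15/18 = 83.3% |
| 7 | 2 | 13/14 = 92.9% | 12/14 = 85.7% |
| 7 | 3 | 20/21 = 95.2% | 18/21 = 85.7% |

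Counting sets restores some tolerance and makes a value near 95% possible. A wholly missed machine still fails the session.

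**5. Illustration only.** Assume full attendance and that each exercise is completed independently with probability *p*. The expected share of adherent sessions is *p*^*m*. At *p* = 0.95 it is 73.5%, 69.8% and 66.3% for 6, 7 and 8 exercises; at *p* = 0.90 it is 53.1%, 47.8% and 43.0%. The values of *p* and the independence are assumptions, not figures from the article.

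**The case against.** The strongest reply is that the rule is strict but usable, and that requiring every station is a legitimate definition. That stands. A reader might infer that the rule cannot be applied, or that it leaves no tolerance at all. The article does not support either reading: a resident who does 9 of 10 repetitions on every machine is fully adherent, so the all-or-nothing character applies to the count of exercises and not to the work done.

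Second, the units are not settled. The 86% example speaks of adhering to a percentage of the intervention, which could mean a share of sets or repetitions, and on that reading 95% is attainable. This stands in part. The words "and then the number of exercises for which there was a 90% adherence" point to whole exercises, and a skipped machine fails on the set count too.

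Third, the session protocol is in Fig. 3, which is not shown. If it adds counted exercises to make ten or more, one miss would be tolerated. This limits certainty, but nothing in the text indicates it.

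Fourth, the harm is easily overstated. A reader might take adherence to be a primary outcome, or suppose that residents will routinely skip a machine. The article says neither: adherence is one assessment method alongside interviews and focus groups, no progression threshold in the article depends on it, and the frequency of skipping is not discussed. The underlying repetition and set records are also kept, so absence and omission are merged only in the summary rate. Finally, misses from a sore joint would cluster within the same people and machines, so the independence illustration does not predict the result.

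**Conclusion.** The point holds as a minor one. Counting whole exercises, with six machines as stated, seven as listed or eight if the last is split, the 90% session threshold is the same as requiring all of them: one miss leaves 83.3%, 85.7% or 87.5%. The article's own 95% and 80% sessions cannot arise on that count. In the clearest case, a resident who does 83.3% of the exercises at full attendance is scored 0%, the same as a non-attender, which distorts the use of the rate as a sign of how demanding the programme is.

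This rests on equally weighted exercises and on fewer than ten counted per session. It does not show that observed adherence will be greatly understated; that depends on how often residents miss a machine, which the article does not give.

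**What to change.** - Reconcile the stated six machines with the seven listed, and say whether abduction and adduction count as one exercise or two.
- State the unit in which session adherence is counted: exercises, sets or repetitions.
- Reconcile the 42-session worked example with the 21 sessions of this study, and use session values that can occur.
- Report adherence as exercises meeting the repetition rule ÷ exercises prescribed, averaged over the 21 sessions, with attendance shown separately. In the example above this gives 83.3% adherence with 21/21 attendance for one resident, and 0% with 0/21 for the other.
- If a yes/no session rule is kept, write it as a number of exercises so that its strictness is plain. How strict to make it is the investigators' choice.

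The cost is a change of wording. The Intervention section says the machines already store repetitions, sets and loads for each user, so no new data are needed. The small downside is two adherence figures in place of one.

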#### Data monitoring

Data will be monitored by the trial management committee at monthly intervals. Prior to analysis, data entry checking will be conducted for accuracy on 10% of all participants, and queries will be resolved through discussion with the trial management committee and access to the source documents held at the university. Data management will adhere to the PANINI data management plan, which was developed in accordance with national and European principles as part of the university research governance and European Commission research governance principles. Thus, data management for this project adheres to the FAIR principles [33].

#### Sample size

This study aims to recruit a convenience sample of *n* = ~ 48 participants: 24 intervention and 24 regular care control. No formal power calculations were conducted due to the feasibility nature of this study. This estimated sample size is based on optimistic projections following preliminary discussion with care home residents with relation to potential uptake.

### Statistical methods

#### Qualitative analysis

Analysis of the feasibility outcomes of this study will be based on an inductive process, which utilises Interpretative Phenomenological Analysis (thematic analysis). Two researchers will be employed to analyse the data acquired in order to increase triangulation from the analysis perspective, having already triangulated data acquisition through data obtainment from multiple sources (i.e. study participants, intervention implementers and study support staff). All semi-structured interviews and focus groups will be audio-recorded. Data synthesis will be performed through verbatim transcription of the semi-structured interviews and focus groups. The three main steps of Interpretative Phenomenological Analysis will be followed [22]: (1) the generation of themes from transcripts within the areas of feasibility inquiry. As an iterative process, these themes will be continuously reviewed and adapted based on the emergence of information in subsequent transcripts. (2) The collation and separation of these themes within each of the areas of feasibility inquiry. (3) Written interpretation of the resultant themes within each of the areas of feasibility and their relationship to one another. At all stages within this process, reflective journal entries and field notes will be utilised to provide a more comprehensive understanding of the findings, in addition to incorporating additional feasibility information related to uptake and retention rates, and limited-efficacy testing of the patient-centred outcomes in the final analysis to provide a comprehensive assessment of the feasibility of the study.

#### Quantitative analysis

Statistical analysis of the patient-centred outcomes will be performed using IBM SPSS (Statistical Package for Social Sciences) software. These analyses will be performed as part of the limited-efficacy testing regarding the potential impact of the intervention on the patient-centred outcomes (proposed primary dependent variables of the future clinical trial). Specifically, for this research, the type of statistical analysis which will be used will be as follows: 2 × 3-way independent measures ANOVA’s (analysis of variance consisting of a two independent variables; the specialised resistance training intervention, and control group, each with three levels: baseline, post-intervention (6 weeks) and follow-up (12 weeks) will be carried out for all patient-centred outcomes. A subsequent post-hoc test will be utilised if a significant main effect or interactions are found. Pearson product correlations will also be utilised between various socio-demographic variables (such as age and sex) and the patient-centred outcomes of this study to assess possible relationships between differences in these socio-demographic factors and changes in the patient-centred outcomes of the study.

Central tendency and variability measurements consisting of the measurement of parameters such as the mean, median and mode, and standard deviation and range of scores respectively, will also be utilised during the analysis of data for illustrative purpose. Significance levels will be set at 0.05 (*p* ≤ 0.05), and effect sizes will be reported for all analyses. Additionally, in order to establish if the assumptions of parametric statistics have been met in relation to the assumption that there is a normal distribution of data, the data will be analysed for skewness and kurtosis. As the quantitative component of this study has not been powered given the feasibility nature of the study, the examination of the efficacy of the intervention to impact these variables is limited and interpretation treated with caution pending the results from the future powered clinical trial. All results will be reported with 95% confidence intervals.

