### Design overview

This feasibility study will utilise a 12-week, interventional, randomised, and independent measures research design (Fig. 1).

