In order to ensure this present study is as scientifically valid as possible a number of precautions have been taken to protect the internal and external validity of the study within its methodological design. First, for each participant, all testing procedures (baseline, post-intervention (6 weeks) and follow-up (12 weeks)) will be conducted at approximately the same time of day (± 2 h). This will be controlled in order to protect the findings of the study from changes in the patient-centred outcomes which may be attributable to circadian variation rather than manipulation of the independent variable [19]. The hypothesis of the study will not be divulged to participants prior to or during the conduction of the study in order to control for any potential degree of demand characteristics; a scenario where participants alter their behaviour and/or answers, in order to align with what they believe is potentially the ‘desired’ outcome of the study. All testing sessions related to patient-centred outcomes will take place at least 24 h after the cessation of the previous training session for each participant. This will be implemented in order to ensure acute fatigue does not only become a contributing factor to the results of the study, specifically relating to the patient-centred outcomes, but also the feasibility of such practice during a proposed future clinical trial. All participants will also be asked to refrain from any relatively high-intensity exercise training up to 24 h prior to each testing session. Due to an independent measures research design being employed, a control group will be employed in order to increase the internal validity of the study, i.e. increases the likelihood that any potential changes in the patient-centred outcomes of the intervention group are due to the intervention and not additional external factors. The order in which patient-centred outcomes are tested will be counter-balanced throughout the study at each assessment time point in order to attempt to protect the study from practice effects, especially in the form of order effects, where a participant has been exposed to a specific order of testing before and as such performs better on subsequent testing procedures of the same material. Stratified-block randomisation of participants (based on frailty score and age) will also be implemented in order to reduce any differences between participants within each of the independent variable groups at baseline. This will also allow for protection against additional threats to the internal validity of the study, such as the influence of passing time (unrelated to the intervention) on participants within the study (maturation), and also protects against potential subconscious selection bias amongst the research team relating to group allocation of participants. Finally, in order to increase the external validity of the study, the eligibility criteria of this present study will be kept as minimalistic as possible (within the limits of safety and reason), in order to allow as inclusive a proportion of this population as possible, and in such producing findings which are applicable to not only those within the study, but to the greater population of frail geriatric older adults within residential care settings.

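### As worded, the efficacy ANOVA treats three repeated measurements on each resident as independent, so its F-tests and pooled-error intervals use the wrong error term

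*Protocol article*

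**What the plan says.** The Quantitative analysis section of the protocol article names the model: "2 × 3-way independent measures ANOVA’s (analysis of variance consisting of a two independent variables". It presents the intervention and the control group as those two variables, "each with three levels: baseline, post-intervention (6 weeks) and follow-up (12 weeks) will be carried out for all patient-centred outcomes". Post-hoc tests follow any significant main effect or interaction. The significance level is 0.05, and effect sizes and 95% confidence intervals are promised throughout. The only assumption check named is skewness and kurtosis, for normality.

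On who is measured and when, the Design overview says "for each participant, all testing procedures (baseline, post-intervention (6 weeks) and follow-up (12 weeks)) will be conducted at approximately the same time of day". The Data collection section says that data are "collected at three main time points: baseline, post-intervention, and follow-up".

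The label also appears outside the analysis section. The Design overview calls the study a "12-week, interventional, randomised, and independent measures research design", and adds: "Due to an independent measures research design being employed, a control group will be employed". There it refers to the two separate arms.

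The Sample size section plans "24 intervention and 24 regular care control", with no power calculation.

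**The concern.** The same residents supply all three measurements. The design therefore has one between-participant factor (arm, two levels) and one within-participant factor (time, three levels). The analysis sentence describes neither correctly. It calls the two arms two variables, when they are two levels of one factor, and it attaches to the whole 2 × 3 layout a label that fits only the arm factor.

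An independent-measures ANOVA on this layout has a single pooled error with 138 degrees of freedom, as if 48 × 3 = 144 different people had been measured. Stable differences between residents then stay in the error for time and for arm × time, where they do not belong. The same error is too small for the arm main effect, where those differences matter most.

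Two uses of the results are at stake. Table 1 asks whether six weeks is long enough to give benefit, and says the answer will inform when the future trial tests its participants; that question turns on arm × time. The Qualitative analysis section also feeds the limited-efficacy results into the overall feasibility judgement. In addition, an inflated arm main effect can by itself set off the post-hoc tests.

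**Working it through.** The plan states no power or precision figure to reproduce, so the check compares the stated ANOVA with one that separates the two error strata.

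**Inputs from the article:** 24 residents per arm, 2 arms, 3 time points, alpha 0.05.

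**Assumptions not in the article:** within-person correlation ρ (0 to 0.9), equal variances and equal correlations over time (compound symmetry), complete data on 48 residents, and, for power only, a 0.5 SD arm difference at both 6 and 12 weeks.

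**Degrees of freedom**
- Independent-measures error: 2 × 3 × (24 − 1) = 138.
- Mixed ANOVA: 2 × (24 − 1) = 46 for arm; 46 × (3 − 1) = 92 for time and arm × time. The two sum to 138.

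**Expected mean squares under the null**
- Arm: σ²(1 + 2ρ).
- Time and arm × time: σ²(1 − ρ).
- Pooled error: σ²[46(1 + 2ρ) + 92(1 − ρ)] / 138 = σ².

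The stated ANOVA divides all three effects by about σ². The arm F is therefore too large by a factor 1 + 2ρ (2.0, 2.4, 2.6 at ρ = 0.5, 0.7, 0.8). The time and arm × time F are too small by a factor 1 − ρ (0.5, 0.3, 0.2).

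**Standard errors, stated model relative to correct**
- Change contrasts, 1/√(1 − ρ): 1/√0.5 = 1.41, 1/√0.3 = 1.83, 1/√0.2 = 2.24.
- Arm main effect, 1/√(1 + 2ρ): 1/√2.0 = 0.71, 1/√2.4 = 0.65, 1/√2.6 = 0.62.

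**Simulation, 20,000 trials per setting**

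| ρ (assumed) | Type I error, arm, as stated | Type I error, arm × time, as stated | Power, arm × time, as stated | Power, arm × time, mixed ANOVA |
|---|---|---|---|---|
| 0 | 5.0% | 5.1% | – | – |
| 0.3 | 12.1% | 1.5% | 16% | 30% |
| 0.5 | 16.8% | 0.4% | 10% | 40% |
| 0.7 | 20.9% | 0.01% | 5% | 62% |
| 0.8 | 22.9% | none in 20,000 | 2% | 80% |
| 0.9 | 24.8% | none in 20,000 | 0.4% | 98% |

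Repeat runs at ρ = 0.5 to 0.8 agree within simulation error; for example, the arm type I error at ρ = 0.8 lies between 22.5% and 22.9%. The mixed ANOVA kept all three type I errors between 4.8% and 5.3% at every ρ. The two analyses agree only at ρ = 0.

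**The case against.** The strongest reply is that this is a slip of wording. The Design overview uses the independent-measures label for the two-arm comparison, and the analysis section may simply have carried it over. Its parenthesis describes two groups each followed over three times, which is the layout of a mixed ANOVA, and the same paragraph speaks of changes in the outcomes. That is plausible, and a reader should not infer that the investigators have decided to treat 144 measurements as 144 people. But no within-participant factor, repeated-measures term or sphericity check appears anywhere, and an analyst following the sentence would run the wrong procedure. Nor is this a detail left to a fuller document: the article itself fixes the model.

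Three stronger readings are tempting and are not supported.
- *Every p-value and interval in the study is wrong.* The Pearson correlations do not use the ANOVA error, nor does a between-arm comparison using one time point's data alone. With complete data, the cell means and mean differences are also unaffected; only their stated uncertainty is.
- *False claims of a treatment effect rise to about 20%.* That figure belongs to the arm main effect, which averages over baseline and is not the treatment effect. The arm × time test errs towards missing a benefit.
- *The study's main purpose is undermined.* Feasibility is the primary aim. Efficacy testing is secondary and unpowered, the article urges caution in reading it, and no progression rule in the article depends on a p-value.

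The last point lessens the consequence. It does not remove the error, because a caution about low power concerns imprecision and not an incorrect error term.

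**Conclusion.** The concern holds for the ANOVA as worded: its F-tests, and the contrasts and confidence intervals that use its pooled error, do not match the repeated-measures data that the article describes. The direction is the same for any positive within-person correlation: the arm main effect is anti-conservative, and time and arm × time are conservative.

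The size rests on the assumed correlation, compound symmetry and complete data. Over 0.5 to 0.8, the arm type I error is about 17% to 23%, the arm × time type I error is 0.4% or less, and standard errors of change contrasts are 1.4 to 2.2 times too large. The power figures rest on the assumed 0.5 SD effect as well, and illustrate the loss in a study that claims no power.

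The sentence should be corrected before analysis, whether it reflects a choice of model or a mislabel.

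**What to change.** Replace the model sentence in the Quantitative analysis section with, for example: *Each patient-centred outcome will be analysed with a 2 (arm, between participants) × 3 (time: baseline, 6 weeks, 12 weeks, within participants) mixed ANOVA with sphericity correction. The effect of interest is arm × time, reported as the between-arm difference in change from baseline at 6 and at 12 weeks with 95% confidence intervals.*

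An equivalent linear mixed model, with arm, time and arm × time as fixed effects and repeated measures within participant, is an acceptable alternative and uses all available observations when a visit is missed. The error itself does not require ranking one time point above the other.

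The cost is one sentence of wording. The data and the SPSS software stay the same, and no extra participants are needed.

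### The efficacy ANOVA uses each outcome's baseline as a response level and never as a covariate, which costs precision and leaves chance baseline imbalance in the reported effect sizes

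*Protocol article*

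**What the plan says.** The Quantitative analysis section of the protocol article names one model for the limited-efficacy testing: "2 × 3-way independent measures ANOVA’s (analysis of variance consisting of a two independent variables", being intervention and control, "each with three levels: baseline, post-intervention (6 weeks) and follow-up (12 weeks) will be carried out for all patient-centred outcomes". It continues: "A subsequent post-hoc test will be utilised if a significant main effect or interactions are found". Effect sizes are to be reported for all analyses, with 95% confidence intervals, and "Significance levels will be set at 0.05".

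The baseline values exist for every resident assessed. Under Baseline assessment, "information for the patient-centred outcomes of the study will be collected between 12 days and 36 h prior to the commencement" of training. Under Data collection, data are "collected at three main time points: baseline, post-intervention, and follow-up".

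The article describes no adjustment for an outcome's own baseline. Covariates are mentioned only under Randomisation and concealment, for the stratification on frailty score and age. The planned Pearson correlations concern socio-demographic variables.

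The planned size is "24 intervention and 24 regular care control", and "No formal power calculations were conducted due to the feasibility nature of this study".

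**The concern.** In a randomised comparison the baseline value cannot be affected by treatment. Used as a covariate, it explains outcome variance and corrects for chance imbalance. Used as a third response level, it does neither efficiently, and it enters the group main effect as a time point at which the true arm difference is zero.

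This would remain if the independent-measures label were corrected to a mixed ANOVA with the resident as the repeated unit, so the check below assumes that correction.

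What is at stake is the quality of the estimates. Potential efficacy is the study's secondary aim, and its results are meant to inform the future trial, including when to test (Table 1, limited-efficacy testing). With about 48 residents, precision is scarce, and stratifying on frailty score and age only partly limits imbalance in outcomes such as cortisol, depression score or cognition.

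**Working it through.** **Inputs from the protocol.** 24 per arm; visits at baseline, 6 and 12 weeks; significance level 0.05, treated as two-sided. The protocol states no power, effect size, SD or dropout, so it has no figure of its own to reproduce.

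**Assumptions.** SD 1 at each visit; equal correlation rho between visits (0.3, 0.5, 0.7); effect 0.65 SD at week 6, with three patterns at week 12; no dropout.

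**1. Group main effect.** It averages the arm difference over three visits. With a true difference of 0, d, d, the expected value is (0 + d + d)/3 = 2d/3. The interaction depends on differences between visits and is not diluted.

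**2. Chance baseline imbalance.** The standard error of the baseline arm difference is sqrt(1/24 + 1/24) = sqrt(2/24) = 0.289 SD. Given an imbalance b, the expected shift is rho × b in a raw week-6 or week-12 contrast, and (rho − 1) × b in a change-from-baseline contrast. ANCOVA removes it in expectation. For b = 0.289:

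| rho | raw contrast | change contrast |
|---|---|---|
| 0.3 | +0.09 | −0.20 |
| 0.5 | +0.14 | −0.14 |
| 0.7 | +0.20 | −0.09 |

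**3. Variance of the week-6 arm contrast.** Relative to a raw variance of 1, the change contrast has 2(1 − rho) and ANCOVA has 1 − rho². ANCOVA is therefore 1 − rho² of the raw variance, and (1 − rho²)/[2(1 − rho)] = (1 + rho)/2 of the change variance. For rho = 0.3, 0.5, 0.7 these ratios are 0.91, 0.75, 0.51 and 0.65, 0.75, 0.85. At rho = 0.5 the confidence interval is sqrt(0.75) = 0.87 times as wide as the raw one, before the small cost of one degree of freedom.

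**4. Power, by simulation** (24 per arm, 0.65 SD at week 6):

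| Test | rho 0.3 | rho 0.5 | rho 0.7 |
|---|---|---|---|
| Raw week-6 contrast | 60% | 60% | 60% |
| Week-6 ANCOVA | 63% | 71% | 86% |
| Interaction (2 df), same effect at week 12 or none left | 48% | 63% | 85% |
| Interaction (2 df), effect halved at week 12 | 37% | 50% | 73% |

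Under no effect, every method rejected in about 5% of simulated trials.

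**The case against.** The strongest reply is that this is a choice between valid analyses. Type I error is held, and randomised contrasts are unbiased over repetitions. The protocol says that efficacy is unpowered and to be read with caution. That stands, and it rules out reading the point as a claim that the planned test is invalid.

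Second, a reader might infer that the plan shrinks the treatment effect by a third throughout. It does not. The treatment test in a group-by-time ANOVA is the interaction, which is undiluted. The dilution matters only because the plan also lets a main effect trigger post-hoc tests and reports effect sizes for all analyses.

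Third, a reader might infer that a post-hoc arm comparison carries the whole baseline imbalance. It carries rho times the imbalance, or (rho − 1) times it for change scores. The article does not say which contrast the post-hoc test uses, a detail that may sit in a fuller plan. Neither form removes the imbalance unless rho is 0 (raw) or 1 (change).

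Fourth, much larger power gains can be shown, but only for ANCOVA on the mean of weeks 6 and 12. At rho = 0.5 that test has about 87% power if the effect is constant, against 63% for the interaction if it is gone by week 12, where the mean-based test falls to about 33%. Formal training ends after week 6 and Table 1 leaves sustained benefit open, so the documents do not support a constant-effect headline.

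Finally, the week-6 ANCOVA figures are for one contrast. If both visits are tested with a Bonferroni correction and the effect is gone by week 12, power is about 52, 61 and 79% at rho = 0.3, 0.5 and 0.7, against 49, 63 and 85% for the interaction. As a yes/no test the interaction is therefore a fair competitor. The case for adjustment rests mainly on the estimates and their intervals.

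**Conclusion.** The point holds as a matter of precision and of how effect sizes are estimated. The two-thirds dilution of the group main effect and the 0.29 SD standard error of the baseline difference follow by arithmetic from the stated design and numbers. The power figures rest on assumed effects, equal correlations and no dropout.

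Against a raw week-6 contrast, adjustment gains about 3, 11 and 26 percentage points at rho = 0.3, 0.5 and 0.7. Against the interaction with a constant effect, it gains about 15, 8 and 1 points (63 − 48, 71 − 63, 86 − 85), so little at rho of about 0.7 or more. If the effect is halved by week 12, the gain is about 26, 21 and 13 points (63 − 37, 71 − 50, 86 − 73).

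The change is worth making because the data are already collected and the estimates are meant to inform the next trial. It is modest in weight because efficacy is secondary and unpowered.

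**What to change.** In the Quantitative analysis section, remove baseline from the outcome levels. For each patient-centred outcome, model the week-6 and week-12 values with terms for arm, visit, arm by visit and that outcome's own baseline value, ideally also baseline by visit, with the resident as the repeated unit. ANCOVA at each visit is an acceptable alternative, and both run in SPSS. Report the baseline-adjusted arm difference at each visit with its 95% confidence interval as the effect size for the future trial, and keep the three-time-point means as description.

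The same rewrite can replace the independent-measures wording. The cost is one degree of freedom, or two with baseline by visit, and a change of analysis wording. No new data, visits or participants are needed.
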